### Study Phases

#### Phase 1: Formative and Baseline Assessment

Phase 1 is primarily meant for desk review and baseline assessment of uptake patterns of modern contraception, along with the determinants of discontinuation within 6 months at the FP service delivery points across the district. Mapping of existing counseling strategies used by the service providers to support contraceptive uptake was done through an extensive literature review in the initial phase [26]. The data collected in this phase will be considered as a point of reference for evaluating the effectiveness of the interventions.

Women of reproductive age seeking FP services or who have recently started using contraception were enrolled. Women visiting centers for emergency contraception or who discontinued use due to systemic illness were excluded from the study.

A pretested, structured questionnaire comprising demographics, reproductive history, contraceptive use, and service use was used for collecting data. Key variables included currently used contraceptive methods, duration of use, reasons for selection, and factors contributing to discontinuation (if applicable). Additionally, facility records from selected centers were reviewed to validate the client-reported data and assess aggregate service use metrics.

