### Study Aim

Broadly, this study aims to evaluate the effectiveness of 3 contraceptive counseling approaches in improving modern contraceptive uptake in FHCs across Rawalpindi, Pakistan: sensitization, GATHER, and the BCS. Specifically, the study will determine the impact of each counseling intervention on modern contraceptive uptake, client satisfaction, and service provider competence at 3 and 6 months after the intervention; conduct a cross-sectional baseline analysis to examine sociodemographic, cultural, and health system factors associated with contraceptive use and discontinuation; identify key barriers and facilitators to contraceptive uptake through integrated quantitative and qualitative methods; compare uptake trends and determinants of contraceptive adoption between intervention and control groups; and generate context-specific evidence to inform the integration of scalable, rights-based counseling models into Pakistan’s national FP programs.

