### Sampling Methods and Sample Size Calculation

#### Consecutive Sampling of Clients

In this initial phase, all eligible clients visiting selected tertiary care hospital–affiliated FHCs will be enrolled through nonprobability consecutive sampling. The sample size for this phase was calculated using the WHO sample size calculator [24], with a margin of error of 0.05, 95% CIs, and assumed prevalence of modern contraceptive uptake of 27%, as reported for Punjab in the Pakistan Demographic and Health Survey 2017‐18. A sample size of 333 participants was calculated using these parameters.

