## Results

Although registration was submitted prior to commencement of the study, administrative processing by the registry was finalized on July 16, 2025, one day after the originally projected start date (July 15, 2025). The registry therefore lists the trial as retrospectively registered. Importantly, no participants were enrolled prior to registration. Recruitment of FP workers began on July 20, 2025, after the completion of concurrent national dengue and polio health campaigns that had temporarily reassigned staff.

Recruitment of clients (n=333) and 48 service providers took place between July 20 and 31, 2025, followed by face-to-face training (July 31 to August 3, 2025) and eHealth knowledge reinforcement via WhatsApp groups (August 1‐31, 2025). Preintervention client satisfaction data were collected in July 2025. As of this protocol version (August 31, 2025), the intervention has been completed, and the study is in the observational follow-up period. The first postintervention data collection was scheduled at 3 months (October 2025), with the second postintervention data collection planned at 6 months (December 2025 to January 2026). No outcome data have yet been analyzed.

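### The Phase 1 aim on determinants of discontinuation within 6 months is broader than a sample of clinic attendees, including recent starters and excluding women who stopped for systemic illness, can support

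*Protocol article*

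**What the plan says.** Study Aim lists as a specific objective to "conduct a cross-sectional baseline analysis to examine sociodemographic, cultural, and health system factors associated with contraceptive use and discontinuation". The section on Phase 1 (Formative and Baseline Assessment) gives the target a time frame and a geographic scope. It covers uptake patterns, "along with the determinants of discontinuation within 6 months at the FP service delivery points across the district".

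For this phase, "all eligible clients visiting selected tertiary care hospital–affiliated FHCs will be enrolled through nonprobability consecutive sampling". On eligibility, the Phase 1 section says: "Women of reproductive age seeking FP services or who have recently started using contraception were enrolled". The next sentence removes a group by its reason for stopping: "Women visiting centers for emergency contraception or who discontinued use due to systemic illness were excluded from the study".

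The questionnaire covers the current method, duration of use and, where it applies, the factors behind discontinuation. On records, "facility records from selected centers were reviewed to validate the client-reported data and assess aggregate service use metrics". No follow-up of the Phase 1 women for discontinuation is described, and no tracing of women who did not come back. The Limitations section names small effects, short follow-up, limited training time and the Hawthorne effect, but nothing about who is missing from Phase 1.

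**The concern.** Determinants of discontinuation within 6 months are a property of women who start a method and are then at risk of stopping it. The Phase 1 sample departs from that population in three ways.

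- **Return.** Women who stopped and did not come back cannot be sampled, while users who return for services can.
- **Exposure time.** A woman interviewed weeks after starting has not had 6 months in which to stop. If she is treated as a 6-month continuer, that status reflects only the interview date.
- **Exclusion on the outcome.** Stopping because of systemic illness is one form of the outcome. Removing those women selects on the outcome and cuts one category out of the reasons to be described.

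At stake is what Phase 1 may conclude. Apparent determinants could partly reflect who started recently and who returns to a center. The list of reasons would be incomplete by construction, and the findings would be read as applying to the district.

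**Working it through.** The plan has no discontinuation figure to reproduce. The 333 was sized for uptake, with an assumed 27% and a 5-point margin, not for discontinuation. The core of the check is therefore a comparison of aim and sample.

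| Element | Aim | Sample |
|---|---|---|
| Women | Those at risk of stopping, across the district | Attendees at selected centers |
| Time at risk | 6 months | Unrestricted; recent starters explicitly enrolled |
| Reasons for stopping | All determinants | Systemic illness excluded |
| Non-returners | Part of the target | Outside the frame; records used only for validation and aggregates |

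The third row needs no assumption: it follows from two sentences in the same section.

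The possible size can only be illustrated. **Assumptions not in the documents:** true 6-month discontinuation D of 10% to 40%; a constant hazard; for the exposure-time column, start dates spread evenly over the past 6 months; for the attendance columns, discontinuers attending a half or a quarter as often as continuing users.

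*Exposure time only.* Monthly hazard λ = −ln(1 − D)/6; share already stopped at interview = 1 − (1 − e^(−6λ))/(6λ). For D = 20%: 6λ = −ln(0.80) = 0.2231, so the share is 1 − 0.20/0.2231 = 10.4%.

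*Attendance only.* With relative attendance a, observed share = aD/(aD + 1 − D). For D = 20% and a = 0.5: 0.10/(0.10 + 0.80) = 11.1%.

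| Assumed true D | Exposure time only | a = 0.5 only | a = 0.25 only |
|---|---|---|---|
| 10% | 5.1% | 5.3% | 2.7% |
| 20% | 10.4% | 11.1% | 5.9% |
| 30% | 15.9% | 17.6% | 9.7% |
| 40% | 21.7% | 25.0% | 14.3% |

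*Both together*, D = 20%: 0.104 × 0.5/(0.104 × 0.5 + 0.896) = 5.5%; with a = 0.25, 2.8%.

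*Systemic-illness exclusion alone*, if 10% of stops are for illness and D = 20%: 0.18/(0.18 + 0.80) = 18.4%. The overall share moves little, but that reason disappears entirely.

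These are attenuated prevalences. An association is distorted only if exposure time or return differs between the groups compared. As an extreme example, take two groups with the same true 20%. One consists only of starters spread over the past 6 months (10.4% observed) and the other has been fully observed for 6 months (20% observed). The odds ratio would be (0.104/0.896)/(0.20/0.80) = 0.46 with no real difference. Whether any covariate in this sample behaves that way is not known.

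**The case against.** Several points on the other side are sound.

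- A reader might infer that the objective cannot be answered at all. The documents do not support that. Attendees who stopped earlier and came back can report their reasons by recall, so the survey can describe self-reported reasons among returning women.
- A reader might fault the short recruitment window ("Recruitment of clients (n=333) and 48 service providers took place between July 20 and 31, 2025"). The length of recruitment does not create any of the three problems; a longer cross-section of attendees would share them.
- The plan promises factors and determinants, not a discontinuation rate. The prevalence figures above rest on assumed inputs, and the even-start assumption makes every woman a recent starter, whereas women seeking services are also enrolled with no limit on duration.
- Within 6 months could mean the preceding 6 months rather than the first 6 months of use. On that reading the exposure-time formula does not apply as given. Non-return and the illness exclusion remain.
- The article does not say that recent starters are counted as continuers. Which women enter the denominator may be fixed in a fuller document, and its absence here is not a fault.
- Setting aside medically driven stopping may be reasonable in a counseling study. If so, the aim should carry that restriction.

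What stands is the mismatch between the stated scope and the stated sample, which the Limitations section does not mention.

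**Conclusion.** The point holds as a mismatch of scope. Attendee-only sampling, inclusion of recent starters and exclusion by reason for stopping are all stated in the article, and together they do not support determinants of 6-month discontinuation across the district. They can support a narrower statement about recalled discontinuation among attendees.

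The size of any bias is unknown. The illustrations show that observed discontinuation could be roughly half the true value or less, but only under the assumed rates and attendance.

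Because Phase 1 data are called a point of reference for evaluating the interventions, a reader might infer that the bias reaches the trial comparison. It does not: Study Outcomes lists uptake, client satisfaction and service provider competence, and discontinuation is not among them. The consequence is confined to Phase 1, and correction is worthwhile because it is nearly free.

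**What to change.** 1. In Study Aim and in the Phase 1 section, restate the objective as factors associated with self-reported discontinuation, for reasons other than systemic illness, among women attending the selected centers. State whether the 6 months run from method start or back from the interview.
2. In Limitations, list the three selections: non-returners not sampled, recent starters with incomplete exposure, and illness-related stopping excluded.
3. In the discontinuation analysis, do not count recent starters as 6-month continuers. Where the collected duration of use allows, analyse time from method start with current users censored at interview.
4. Restrict to methods started at least 6 months before interview only if start dates of stopped methods were recorded. Duration of use alone does not give a start date for a woman who has stopped. If the item covers only the current method, steps 1 and 2 are the minimum.

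The cost is wording plus an analysis rule on data already collected. The claim becomes narrower and fewer of the 333 women are informative. No analysis recovers the women who did not return, so the restated scope is needed in every case.

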#### Phase 2: Intervention Using Different FP Counseling Approaches

##### Overview

To evaluate the effectiveness of training interventions in enhancing the counseling skills of FP providers across centers affiliated with tertiary care hospitals, we propose an experimental study design to assess the effectiveness of 2 distinct counseling strategies. This 3-arm, single-blinded, parallel, cluster-randomized study will compare routine care (arm 1) with contraceptive counseling intervention based on GATHER (arm 2) and contraceptive counseling intervention based on the BCS (arm 3); the two interventions use different counseling approaches to provide comprehensive contraception information through a client-centered approach, thus increasing client satisfaction and contraception uptake (Table 1). As part of the study design, clients are blinded to the type of counseling approach they receive to minimize bias in reporting of satisfaction.

**Table 1. T1:** Study arms and corresponding interventions for the randomized clinical trial.

Participant group/arm	Intervention
Control arm 1	Routine contraceptive counseling and routine method availability (sensitization of the service providers for routine counseling)
Experimental arm 2	Counseling intervention A (GATHER^a^) and routine method availability
Experimental arm 3	Counseling intervention B (balanced counseling strategy) and routine method availability

a GATHER: greet, ask, tell, help, explain, return.

##### Randomization and Blinding

Cluster randomization was conducted at the hospital level, with each hospital constituting a cluster. Hospitals with similar characteristics were grouped to maintain comparability, and randomization was performed using computer-generated methods, with stratification to balance key variables such as hospital size and patient demographics. This strategy helps in minimizing contamination and bias in allocation.

For the interventional phase, the interventional arms are implementing the standardized counseling approach for which they were trained, whereas the control arm continues routine practices. Clients will remain blinded to the counseling approach they are provided, but owing to the nature of the interventions, the service providers know which arm they are assigned to. Although this is a study design limitation, it is standard practice in behavioral interventional trials.

##### Implementation of the Intervention

The interventional phase lasts for 3 months. During this period, training on GATHER and the BCS is given to the service providers in the interventional arms. Continuous learning is ensured through refresher courses, mentorship, and supportive supervision. Trained FP service providers will apply the enhanced counseling specific to their arm during routine practice, including during consultation sessions and follow-up care, through a structured, step-by-step guide.

##### Effective Follow-Up Through Technologically Supportive Supervision

To enhance service provider capacity and promote lasting improvements in contraception counseling practices, the study implements a dual approach: an intensive 1-day training session followed by 3 months of supportive supervision combining in-person oversight with technology-assisted follow-up. The 1-day training aimed to quickly establish core knowledge and practical skills in client-centered, rights-based contraception counseling. We acknowledge that a single training event is typically inadequate for sustained behavioral change; thus, we incorporated a structured system of ongoing supportive supervision. This includes regular supervisory visits, on-site mentoring, and direct observation, all intended to deliver immediate feedback, reinforce essential competencies, and address challenges encountered in real-world service delivery.

To supplement the in-person support and enhance both reach and responsiveness, the study incorporates technology-enabled supervision through the establishment of dedicated WhatsApp groups. These groups serve as active forums for peer learning, case-based discussions, and prompt problem-solving, fostering ongoing interaction among service providers, mentors, and supervisors. They enable the regular sharing of refresher materials, such as videos, infographics, and updated guidelines, and provide an interactive environment for exchanging experiences and clarifying uncertainties. By leveraging WhatsApp’s accessibility and ease of use, this approach ensures that service providers remain engaged, supported, and motivated throughout the implementation period. This hybrid model of capacity building, which integrates initial face-to-face training with sustained digital engagement and supervisory support, is proving to be both cost-effective and well suited to the context, thereby promoting strong adherence to the intervention and improving the quality and consistency of contraception counseling across the participating sites.

### Phase 3: Implementation and Scalability

This phase aims to explore the facilitators and barriers associated with the implementation and scalability of the proposed intervention while maintaining a focus on relevance and effectiveness in improving the uptake of modern contraceptives. A qualitative approach will be used to gather insights from service providers and facility managers at FHCs. In-depth interviews will be conducted to explore perceptions of varied aspects of the study, including implementation challenges such as resource limitations, gaps in training, and cultural resistance, as well as views on feasibility and recommendations for improvements.

We will conduct 10 to 12 in-depth interviews with key members in the relevant institutional departments and 2 to 4 focus group discussions with FP providers through purposive sampling to ensure thematic saturation. The anticipated duration of the interviews is 30 to 40 minutes; they will be conducted in a safe and neutral space so as to ensure confidentiality and the comfort of the participants. The interviews will be recorded after the participants provide informed consent. Transcription of the audio recordings and translation into English will be done by research assistants. Accuracy will be ensured through checking the transcripts with audio files.

The transcripts will be coded using thematic analysis, and barriers, facilitators, and opportunities will be identified for scaling up. This phase is expected to generate outcomes leading to actionable insights that will improve the feasibility, acceptability, and scalability of the intervention, contributing to improved uptake. Figure 3 shows the study plan.

**Figure 3. F3:**
[figure not shown]
CONSORT (Consolidated Standards of Reporting Trials) chart. BCS: balanced counseling strategy; FHC: family health center; GATHER: greet, ask, tell, help, explain, return.

### Data Collection and Analysis

Data has been collected from structured facility records and client exit interviews at baseline (before the intervention) and will be collected 3 and 6 months after the intervention. Data quality will be ensured through descriptive statistics and logical validation checks, identifying missing values, inconsistencies, and outliers. The baseline characteristics will be summarized for assessing comparability across clusters.

The quality of FP services will be assessed using the Quick Investigation of Quality tool, which measure 25 key indicators of counseling quality [27]. For the data analysis, SPSS (version 26; IBM Corp) will be used. Service provider and client characteristics will be summarized in descriptive analyses. Exploratory comparisons will use paired 2-tailed *t* tests (or Wilcoxon signed-rank tests), ANOVA, and *χ*^2^ tests.

Mixed effects regression models with a random intercept for hospital catchment (cluster) will be using for clustering. These will be used to analyze binary outcomes of the interventions, such as uptake of modern contraceptives. Mixed effects logistic regression will be applied. For continuous outcomes, such as client satisfaction and quality score, we will use mixed effects linear regression. To assess robustness, population-averaged models using generalized estimating equations with robust SEs will be considered as a sensitivity analysis.

To estimate the changes in outcome over time between the interventional and control arms, we will use a difference-in-differences approach. All multivariate models will be adjusted for individual-level covariates such as age, parity, education, and baseline contraceptive use, as well as facility-level characteristics.

Effect sizes for categorical outcomes will be reported as odds ratios with 95% CIs, and for continuous outcomes, Cohen *d* will be used. Statistical significance will be assessed at a 2-sided *P* value <.05. Results will be presented in the form of tables and graphical summaries for interpretability and for informing future scalability.

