## Methods

### Study Framework

The theory of change construct will be used in this study. Using this theory enables interventions to improve client satisfaction and service provider competency through training and measure these improvements in terms of behavioral change, thereby making FP services more effective. The current trial plans to assess the effectiveness of 3 counseling approaches in improving the uptake of modern contraceptives over a period of 6 months: sensitization, GATHER, and the BCS. The study hypothesis is that contraceptive uptake will differ among the 3 approaches.

The duration of the trial will be 8 to 9 months, structured in 3 phases. The first phase is a formative phase, during which baseline assessments will be obtained. This will be followed by the interventional phase, in which service providers will be given training specific to the study arm they are allocated to. The last phase will be an exploratory phase meant to identify enablers and barriers and other findings that can facilitate the scaling-up of the study. The conceptual framework of the study is shown schematically in Figure 1.

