#### Study Participants: Purposive Sampling and Sample Size Calculation

For the final phase of the trial, women of reproductive age visiting FHCs for FP services will be recruited through purposive sampling to compare client satisfaction and uptake of modern contraceptive methods before and after the intervention. The sample size estimate considered feasibility and the ability to inform future scale-up studies covering larger populations.

Baseline modern contraceptive uptake in all arms was assumed to be approximately 25% based on estimates from the Pakistan Demographic and Health Survey 2017‐18. A collective review of systematic reviews and meta-analyses revealed that improved counseling strategies can increase contraceptive uptake up to 30% to 40%, corresponding to an absolute increase of nearly 8% to 18% in comparison to routine care [23]. Based on the above evidence, we assumed values of 25% and 40% for contraceptive uptake in the control and interventional arms, respectively. An absolute effect size of 15% or 0.15 points was assumed for this study.

The sample size was calculated using a standard formula for comparing 2 populations through testing the 1-sided hypothesis. The significance level was set at 5% (α=.05) for a power of 80% (1−β=0.80). Given the design of the study, a pragmatic approach was used. Consistent with values reported in health services literature, an intracluster correlation coefficient (ICC) of 0.02 [25] and design effect of 1.38 (DE=1+(m-1) x ICC) was applied. Following methodological guidance for pilot trials, the sample size was not inflated to meet confirmatory power requirements, and a sample size of 60 per arm and 180 across all 3 arms was chosen.

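### With only a constant hospital intercept, the difference-in-differences standard error omits hospital-specific change between rounds, so the test is moderately too liberal if hospitals drift differently

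*Protocol article*

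**What the plan says.** Protocol article, Data Collection and Analysis, names one random effect: "Mixed effects regression models with a random intercept for hospital catchment (cluster) will be using for clustering". For binary outcomes, including the primary outcome of uptake, "Mixed effects logistic regression will be applied"; satisfaction and quality score get the linear counterpart. The next paragraph gives the effect of interest: "To estimate the changes in outcome over time between the interventional and control arms, we will use a difference-in-differences approach". Data come from facility records and "client exit interviews at baseline (before the intervention) and will be collected 3 and 6 months after the intervention", so there are three rounds. The same section plans adjustment for client and facility covariates and a two-sided 5% level. It adds that "population-averaged models using generalized estimating equations with robust SEs will be considered as a sensitivity analysis".

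Randomisation and Blinding makes each hospital a cluster, and Study Framework states the hypothesis: "The study hypothesis is that contraceptive uptake will differ among the 3 approaches". Neither the number of hospitals nor any correlation of hospital effects between rounds is given. No hospital-by-round or random time effect is named anywhere.

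**The concern.** A hospital intercept that is constant over time drops out when a hospital's baseline level is subtracted from its follow-up level. What remains in the error of the arm-by-time term is sampling noise between clients. Since whole hospitals were allocated, the relevant error also includes how much one hospital's change differs from another's for reasons unrelated to counselling. The specified model sets that component to zero.

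Such differences are plausible here. In the first phase, "all eligible clients visiting selected tertiary care hospital–affiliated FHCs will be enrolled through nonprobability consecutive sampling", whereas for the before-and-after comparison "women of reproductive age visiting FHCs for FP services will be recruited through purposive sampling"; client mix could therefore shift differently from site to site. The Results section also reports that health campaigns had drawn staff away shortly before recruitment. If hospitals do drift, confidence intervals for uptake, satisfaction and quality score are too narrow, and local drift can pass for a counselling effect. That would mislead the larger trial this pilot is meant to inform.

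**Working it through.** **The plan's own figure.** Sampling Methods and Sample Size Calculation gives an ICC of 0.02 and a design effect of 1.38. From 1 + (m − 1) × 0.02 = 1.38, m = 20. With 60 clients per arm, 60/20 = 3 hospitals per arm, so 9 in all. The figure reproduces, but the hospital count is implied, not stated.

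**Inputs**
- Follow-up clients per hospital: m1 = 20. This assumes the 60 per arm applies at each follow-up round.
- Baseline clients per hospital: m0 = 333/9 = 37. This assumes an equal split.
- ICC = 0.02 (protocol); 0.05 is an added assumption, for example for provider-driven scores.
- CAC, the correlation of a hospital's effect between rounds: not stated, so shown as a range.
- New clients at each round (assumption).

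**Formula.** Take total variance as 1. The client part is 1 − ICC, and the round-specific hospital part is ICC × (1 − CAC). Per hospital, the variance of change is (1 − ICC)(1/m0 + 1/m1) + 2 × ICC × (1 − CAC). The intercept-only model counts just the first term, so the ratio of true to modelled variance is

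R = 1 + 2 × ICC × (1 − CAC) / [(1 − ICC)(1/m0 + 1/m1)],

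and the actual size of a nominal two-sided 5% test is 2 × [1 − Φ(1.96/√R)].

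**Numbers.** 1/37 + 1/20 = 0.0770. At ICC 0.02 the denominator is 0.98 × 0.0770 = 0.0755; at CAC 0.5 the numerator is 2 × 0.02 × 0.5 = 0.02. So R = 1 + 0.02/0.0755 = 1.265, 1.96/√1.265 = 1.743, and the size is 8.1%. The simulation column comes from logistic models with one intercept per hospital, up to 4,000 null trials per setting.

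| ICC | CAC | R | Size, formula | Size, logistic simulation |
|---|---|---|---|---|
| 0.02 | 1 | 1.000 | 5.0% | 5.2% |
| 0.02 | 0.8 | 1.106 | 6.2% | 6.2% |
| 0.02 | 0.5 | 1.265 | 8.1% | 8.4% |
| 0.02 | 0 | 1.530 | 11.3% | 11.4% |
| 0.05 | 0.8 | 1.273 | 8.2% | 8.1% |
| 0.05 | 0.5 | 1.683 | 13.1% | 13.2% |

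The row at CAC 1 shows that the test holds its level when hospital effects are constant over time.

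**Other hospital counts** (formula, ICC 0.02, CAC 0.8 and 0.5)
- 6 per arm (18 baseline, 10 follow-up clients each): 5.6% and 6.5%.
- 2 per arm (55 and 30): 6.9% and 9.7%.
- 1 per arm (111 and 60): 8.8% and 14.3%.

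**Check of the remedy.** Comparing arms on hospital-level changes with a t test gave 4.8% to 5.1% in every simulated setting with at least 2 hospitals per arm. With 1 per arm, hospital drift and arm effect cannot be separated.

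**The case against.** **Degrees of freedom.** A reader might infer that a small-sample correction to the intercept-only model would not help. At the protocol's ICC that is wrong for a single contrast. With a t reference on 9 − 3 = 6 degrees of freedom (critical value 2.45), the size is 1.4%, 2.0%, 3.0% and 4.8% at CAC 1, 0.8, 0.5 and 0. This is one error offsetting another: the test is very conservative at CAC 1, and at ICC 0.05 with CAC 0.5 it is back above nominal, at 5.9%. The protocol names no such correction.

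**Omnibus test.** A joint test over three arms and two follow-up rounds would show larger inflation. The protocol names no such test, so those rates should not be used to size the problem.

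**Same clients followed.** The planned paired tests, adjustment for baseline contraceptive use and mention of loss to follow-up suggest some clients are seen repeatedly; purposive recruitment suggests otherwise. If the 20 follow-up clients are among the 37 at baseline, a model without a client effect overstates the client part. The two errors cancel when the within-client correlation is 37 × ICC × (1 − CAC)/(1 − ICC): 37 × 0.004/0.98 = 0.15 at CAC 0.8 and 37 × 0.01/0.98 = 0.38 at CAC 0.5. So the direction of the error depends on a point the document leaves open.

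**Covariates.** The planned adjustment may absorb part of a client-mix shift. It cannot be relied on for staffing or supply changes, and its effect is not quantified here.

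**Cover elsewhere.** Robust-error GEE would in principle allow for hospital-by-round shifts, but it is optional, secondary and itself liberal with about nine clusters. The promise to account for clustering under Quantitative and Qualitative Analysis and Integration adds no term. The difference-in-differences sentence stands in its own paragraph, and a fuller plan could add a component; but this article does fix the random-effects structure and offers no other primary clustered model.

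**Pilot status.** The sample was not inflated for confirmatory power and the findings are called exploratory. That lowers the stakes, but the objective is still to compare effectiveness, at a 5% significance level.

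**Conclusion.** The stated random-effects structure is incomplete for a difference-in-differences analysis with hospitals randomised. Under 3 hospitals per arm, new clients each round and ICC 0.02, a nominal 5% contrast at 6 months has a true size of about 6% at CAC 0.8, 8% at 0.5 and 11% at 0. At an assumed ICC of 0.05 it is about 8% and 13% at CAC 0.8 and 0.5. This is a moderate excess, near nominal if hospital effects are almost constant over time and larger with fewer hospitals. CAC, hospital count and separate client samples are assumptions.

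A reader might also infer that the model tests a different hypothesis, namely that every hospital changes identically. The documents do not support that: the tested parameter is still the arm-by-time term, and it is the reference distribution that is too narrow.

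**What to change.** In Data Collection and Analysis, for every model with an arm-by-time term (logistic for uptake, linear for satisfaction and quality score), specify random intercepts for hospital and for hospital-by-assessment-round, with cluster-level small-sample degrees of freedom. State the number of hospitals per arm and whether the same clients are followed.

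A fallback is needed. With 9 hospitals and 3 rounds, the added variance rests on (9 − 3) × (3 − 1) = 12 degrees of freedom. In a balanced linear approximation with about 24 clients per hospital and round, at ICC 0.02, it would be estimated at zero in about 46% of trials at CAC 0.8 and 35% at CAC 0.5, which returns the intercept-only model. Prespecify instead, for that case, a comparison between arms of each hospital's change from baseline (one value per hospital and follow-up round) with a t or F reference, ideally pooling variance over all three arms. This needs at least 2 hospitals per arm.

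The change needs no new data, and at the article's version date no outcome data had been analysed. The cost is one more variance term and noticeably wider intervals. The critical value rises from 1.96 to 2.45 with 6 degrees of freedom (2.45/1.96 = 1.25) or to 2.78 with 4 (2.78/1.96 = 1.42). That is the honest precision of the design and acceptable in a pilot.
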